**Figure 3 figure3:**
[figure not shown]
Flow diagram.

### Participants

To be eligible for study participation, a participant must meet all of the following criteria: (1) age 7-17 years (inclusive); (2) primary Diagnostic and Statistical Manual of Mental Disorders (DSM)-5 diagnosis of OCD; and (3) CY-BOCS score ≥16.

A potential participant meeting any of the following criteria will be excluded from participation: (1) a psychiatric comorbidity that has a higher treatment priority than OCD and makes participation clinically inappropriate (eg, primary anorexia nervosa, depression with suicidality, and psychosis); (2) mental retardation (if suspected based on the level of functioning, or in the presence of neuropsychiatric comorbidity, an IQ test is performed); and (3) insufficient understanding of the Norwegian language.

### Assessments

Assessments are performed pretreatment and posttreatment, and at 3- and 6-month follow-ups. A 12-month follow-up assessment is envisioned.

### Outcome Measures

Outcome measures for treatment acceptability, feasibility, and effectiveness are specified below. Table 1 provides an overview of the assessments. Acceptability involves the following: Client Satisfaction Questionnaire-8 (CSQ-8) [35], primary outcome; a treatment evaluation questionnaire for children and their parents composed of the User Experience Questionnaire (UEQ) [36], and qualitative and quantitative treatment-specific questions; a modified version of the Barriers to Treatment Participation Scale (BTPS) [37], child and parent version (for the aim of this study, we shortened the questionnaire, added a child version, and adapted some items to increase the fit to the eCBT treatment package); and a short qualitative interview examining clinicians’ treatment satisfaction and their suggestions to improve the treatment. Feasibility involves the following: preterm treatment drop out, primary outcome; and number of eligible participants that rejected/accepted eCBT. Effectiveness involves the following: CY-BOCS [38], primary outcome; Child Obsessive-Compulsive Impact Scale-Revised (COIS-R) [39]; and Family Accommodation Scale for OCD–Self-Rated Version (FAS-SR) [40]. Comorbidity/psychological well-being involves the following: Strengths and Difficulties Questionnaire (SDQ) [41]; Child Behavior Checklist (CBCL) [42]; Youth Self-Report Questionnaire (YSR) [42]; Screen for Child Anxiety-Related Emotional Disorders-Revised (SCARED-R) [43,44]; Mood and Feelings Questionnaire (MFQ) [45]; KINDL-R [46]; Children’s Global Assessment Scale (CGAS) [47]; and Clinical Global Impressions Scale-Severity/Improvement (CGI-S, CGI-I) [48]. Other study parameters include the following: study-specific *treatment integrity forms* completed by the therapist following each treatment session and the Trimbos/iMTA Questionnaire for Costs associated with Psychiatric Illness (TiC-P) [49].

**Table 1 table1:** Overview of assessments.

Assessment	Pretreatment	During treatment	Posttreatment	Follow-up 3 months	Follow-up 6 months
CY-BOCS^a^	IE^b^	N/A^c^	IE	IE	IE
CGI-S^d^	IE	N/A	IE	IE	IE
CGI-I^e^	N/A	N/A	IE	IE	IE
CGAS^f^	Therapist	N/A	Therapist	Therapist	Therapist
COIS-R^g^	Child and parent	N/A	Child and parent	Child and parent	Child and parent
FAS^h^	Parent	N/A	Parent	Parent	Parent
CBCL^i^	Parent	N/A	Parent	N/A	Parent
YSR^j^	Child (≥11 years)	N/A	Child (≥11 years)	N/A	Child (≥11 years)
SCARED^k^	Child and parent	N/A	Child and parent	Child and parent	Child and parent
MFQ^l^	Child and parent	N/A	Child and parent	Child and parent	Child and parent
SDQ^m^	Child and parent	N/A	Child and parent	Child and parent	Child and parent
KINDL	Child and parent	N/A	Child and parent	Child and parent	Child and parent
CSQ-8^n^	N/A	N/A	Child and parent	N/A	N/A
Treatment evaluation questionnaire	N/A	N/A	Child and parent	N/A	N/A
BTPS^o^ (modified version)	N/A	N/A	Child and parent	N/A	N/A
TiC-P^p^	Parent	N/A	Parent	Parent	Parent
Session integrity form	N/A	Therapist	N/A	N/A	N/A

^a^CY-BOCS: Children’s Yale-Brown Obsessive-Compulsive Scale.

^b^IE: independent evaluator.

^c^N/A: not applicable.

^d^CGI-S: Clinical Global Impressions Scale-Severity.

^e^CGI-I: Clinical Global Impressions Scale-Improvement.

^f^CGAS: Children’s Global Assessment Scale.

^g^COIS-R: Child Obsessive-Compulsive Impact Scale-Revised.

^h^FAS: Family Accommodation Scale for obsessive-compulsive disorder.

^i^CBCL: Child Behavior Checklist.

^j^YSR: Youth Self-Report Questionnaire.

^k^SCARED: Screen for Child Anxiety-Related Emotional Disorders.

^l^MFQ: Mood and Feelings Questionnaire.

^m^SDQ: Strengths and Difficulties Questionnaire.

^n^CSQ-8: Client Satisfaction Questionnaire-8.

^o^BTPS: Barriers to Treatment Participation Scale.

^p^TiC-P: Trimbos/iMTA Questionnaire for Costs associated with Psychiatric Illness.

### Statistical Analysis

Regarding feasibility and acceptability, descriptive statistics will be provided as follows: CSQ-8, treatment evaluation questionnaire, and modified BTPS for treatment acceptability, and preterm treatment drop out and number of eligible participants that rejected/accepted eCBT for treatment feasibility.

Regarding effectiveness, the treatment effect is expressed as percentage symptom improvement based on the CY-BOCS, the percentage of patients with OCD symptoms in the clinical range (CY-BOCS ≥ 16) and in remission (CY-BOCS ≤ 12), and the percentage of treatment responders (≥35% symptom reduction on the CY-BOCS plus CGI-I rating of 1 or 2 “[very] much improved”) [50]. Effect size (*d*) is calculated by the mean difference in the CY-BOCS score before and after eCBT divided by the SD of the difference in the score before and after eCBT. We will run a series of linear mixed models with treatment outcome (CY-BOCS, CGAS, COIS-R, FAS-SR, CBCL/YSR, SCARED, and MFQ) as the dependent factor and time as the independent factor. An independent *t* test will be performed to compare the treatment outcome (difference in the CY-BOCS score before and after treatment) in this study with the treatment outcome reported for the NordLOTS [11]. 

In terms of other study parameters, for treatment adherence, treatment integrity forms are evaluated by two raters independently, and Cohen kappa will be calculated. To get an impression of treatment costs, outcomes for the TiC-P (related to the SDQ) will be described.

In case of missing assessments, all possible attempts will be made to contact participants.

For feasibility and acceptability analyses, missing data will be described. Acceptability analyses will be conducted on cases having complete data on these measures after treatment.

Regarding treatment outcome, an algorithm for handling missing data is integrated in linear mixed model analyses. Cases with missing data at baseline will be excluded from analyses.

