### Aims and Hypotheses

The aim of the study is to explore whether eCBT is (1) a feasible intervention in terms of treatment drop out; (2) an acceptable intervention; and (3) an effective intervention for children and adolescents with OCD in terms of positive treatment outcomes and showing noninferiority to traditional CBT (Nordic Long-term OCD Treatment Study [NordLOTS]) [11] for the primary outcome measure (Children’s Yale-Brown Obsessive-Compulsive Scale [CY-BOCS]).

We hypothesize that (1) preterm treatment drop out will be equivalent or lower than that found for traditional CBT (≤10%) [11]; (2) eCBT will be positively evaluated by children and their parents; (3) there will be a considerable reduction in OCD symptoms after treatment; and (4) the treatment outcome (CY-BOCS) for eCBT will show noninferiority to traditional CBT (NordLOTS) [11].

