## Methods

### Study Design and Sample Size

This study is an open trial using a historical control design to explore the feasibility, acceptability, and effectiveness of eCBT in children and adolescents with OCD. To examine noninferiority of eCBT to traditional CBT, the treatment outcome for eCBT (CY-BOCS) will be compared to data collected in the NordLOTS [11]. The intended sample size is 30 participants.

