### Sample Size

As the intervention concerns an innovative treatment, the study is primarily aimed at studying acceptability and feasibility. For this goal, a power calculation cannot be performed.

To explore noninferiority of eCBT to traditional CBT (as delivered in the NordLOTS), we will use a historical control design. A power calculation (noninferiority margin set at 4 points on the CY-BOCS) shows that 21 participants per treatment arm would be sufficient to show noninferiority (80% power).

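### The t test named for the NordLOTS comparison does not apply the 4-point margin, so the analysis does not match the noninferiority aim or the basis of the sample size

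*Protocol article*

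**What the plan says.** All places are in the Protocol article.

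- **Aims and Hypotheses**, hypothesis 4: "the treatment outcome (CY-BOCS) for eCBT will show noninferiority to traditional CBT (NordLOTS").
- **Study Design and Sample Size**: "To examine noninferiority of eCBT to traditional CBT, the treatment outcome for eCBT (CY-BOCS) will be compared to data collected in the NordLOTS". The same section adds: "The intended sample size is 30 participants".
- **Sample Size**: the power calculation has its "noninferiority margin set at 4 points on the CY-BOCS" and finds that "21 participants per treatment arm would be sufficient to show noninferiority (80% power").
- **Statistical Analysis**: the one analysis named for this comparison is a two-sample t test against the NordLOTS outcome: "test will be performed to compare the treatment outcome (difference in the CY-BOCS score before and after treatment) in this study".

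The Statistical Analysis section does not mention the margin, a shifted null hypothesis, a one-sided level, a confidence interval or a criterion for declaring noninferiority. The linear mixed models in that section have time as their only independent factor, so they do not address the comparison with NordLOTS.

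**The concern.** An independent t test used to compare two means ordinarily takes zero difference as its null hypothesis. Noninferiority is a different question: is eCBT worse than traditional CBT by less than 4 points? The two can disagree in both directions.

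- A nonsignificant result may only mean that the estimate is imprecise. It does not exclude a deficit of 4 points or more.
- A significant deficit may be small and precisely estimated, and so lie wholly within the margin.

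The margin was fixed and used to size the comparison, but the named analysis does not carry it forward. At stake is whether hypothesis 4 gets a controlled answer. If nonsignificance were used as the criterion, a smaller or noisier study would find noninferiority easier to claim.

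**Working it through.** **Inputs.** From the Protocol article: margin 4 points, 21 per arm, 80% power, 30 planned eCBT children. Not stated, and therefore assumed: SD of CY-BOCS change, alpha and sidedness, and number of NordLOTS controls.

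**1. The plan's own figure.** With a true difference of zero, the usual formula is n per arm = 2 × SD² × (z₁₋α + z₀.₈)² / margin². Without SD and alpha, 21 cannot be verified, only solved backwards: SD = 4 × √(21/2) / (z₁₋α + z₀.₈).

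- One-sided 2.5%: 4 × 3.240 / (1.960 + 0.842) = 4.63.
- One-sided 5%: 4 × 3.240 / (1.645 + 0.842) = 5.21.

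So 21 per arm is compatible with a margin-based calculation at an SD of about 4.6 or 5.2. The sample size rests on the margin; the named analysis does not mention it.

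**2. What happens if nonsignificance is used as the criterion.** Let eCBT be truly 4 points worse. The standard error is SD × √(1/n₁ + 1/n₂) and the noncentrality is 4 / SE. The chance of a nonsignificant two-sided 5% test, P(|t| < t_crit), comes from the noncentral t distribution. For example, with SD 4.63 and 30 vs 30, SE = 4.63 × √(2/30) = 1.20, the noncentrality is 3.35, and the probability is 0.092.

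| SD of change | Source | 21 vs 21 | 30 vs 30 | 30 vs 100 |
|---|---|---|---|---|
| 4.63 | implied, one-sided 2.5% | 22% | 9% | 1.5% |
| 5.2 | implied, one-sided 5% | 32% | 17% | 4% |
| 7 | assumed | 56% | 41% | 22% |
| 8 | assumed | 65% | 52% | 34% |

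Comparing a 95% confidence limit with the margin gives 2.5% in every cell. Under the zero-null criterion the rate moves with SD and control sample size.

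**3. The two readings disagree in both directions.** These are illustrations with assumed observed differences.

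- SD 7, 30 vs 30: the half-width of the 95% interval is 3.62. An observed deficit of 3 points is nonsignificant (3 − 3.62 = −0.62), but the upper limit is 3 + 3.62 = 6.62, well beyond 4. Noninferiority is not shown.
- SD 4.63, 30 vs 100: the half-width is 1.91. An observed deficit of 2 points is significant (2 − 1.91 = 0.09), but the upper limit is 2 + 1.91 = 3.91, inside the margin. eCBT is noninferior.

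**4. Power when the margin is applied** (one-sided 2.5%, true difference zero).

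| SD of change | 30 vs 30 | 30 vs 100 |
|---|---|---|
| 4.63 | 91% | 98% |
| 5.2 | 83% | 96% |
| 7 | 59% | 78% |
| 8 | 48% | 66% |

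**The case against.** The strongest reply is that the t test itself is not at fault. A two-sample t procedure can be run against a null shifted by 4 points, or its confidence interval can be compared with 4, and either is still an independent t test. The article states no null hypothesis. Its design section says that the comparison serves noninferiority, and its sample size section fixes the margin in advance. This stands against the stronger reading that the t test cannot answer hypothesis 4. It does not remove the mismatch, because the analysis section says neither of these things and a plain comparison of means ordinarily tests zero difference.

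Second, a reader might infer that p > 0.05 will be reported as noninferiority. No section says so. The false-acceptance figures are therefore conditional: they show what an unstated rule would allow, not what the investigators plan.

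Third, a reader might infer that the error is large throughout. The protocol's own 21 per arm implies an SD of about 4.6 to 5.2. With 100 controls the rate there is 1.5–4%, near or below conventional levels. The large figures need a wider assumed SD or a small control group.

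Fourth, the article condenses a fuller research protocol, and a separate analysis plan may exist. The confidence level and sidedness could properly be left there. But the article does name the test for this hypothesis, and the test as named does not use the margin. That is more than an omitted detail.

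Finally, the Sample Size section puts acceptability and feasibility first and describes the noninferiority comparison as exploratory, and the Discussion names a randomized trial as a future step. This lowers the severity.

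**Conclusion.** The point holds: the analysis named for the NordLOTS comparison does not apply the 4-point margin, and so does not match the noninferiority aim or the basis of the sample size. Neither a significant nor a nonsignificant zero-null result settles hypothesis 4.

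If nonsignificance were taken as noninferiority, the error would be uncontrolled, ranging from about 1.5% to 52% across the 30-child scenarios shown. That range rests on assumed SDs and control sample sizes and on a two-sided 5% test.

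The documents do not support saying that the hypothesis is unanswerable or that a false claim is planned. For an exploratory comparison with a historical control this should be fixed, but it is not a fatal flaw.

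**What to change.** In Statistical Analysis, add a decision rule, for example: *The difference is the NordLOTS mean CY-BOCS reduction minus the eCBT mean reduction. Noninferiority is concluded only if the upper limit of its two-sided 95% confidence interval is below 4 points; otherwise noninferiority is not shown.* The independent t procedure can supply that interval.

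In Sample Size, state the matching alpha (one-sided 2.5%) and the SD used.

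The cost is two or three sentences and no new data. If 21 per arm was computed at one-sided 2.5%, it stands. If it was computed at one-sided 5% (SD about 5.2), the same formula at one-sided 2.5% gives 2 × 5.2² × 2.802² / 4² = 26.5, so 27 per arm. That is still within the 30 planned eCBT children, provided the NordLOTS group has at least as many. The Results section says that data collection is ongoing, so as the article stands the rule can be set before the comparison is run.

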## Introduction

### Background

Pediatric obsessive-compulsive disorder (OCD) is a relatively common, severe, and debilitating condition [1], leading to substantial impairment in family, academic, and social functioning [2,3] and reduced quality of life [4]. Cognitive behavioral therapy (CBT) is the treatment of choice [5,6], and its effectiveness has been extensively demonstrated [7-9]. However, treatment for pediatric OCD is limited by several problems.

First, not all children benefit sufficiently from treatment. In general, after standardized CBT, average symptom improvement is about 50%, with large individual differences [10,11]. The combination of CBT with pharmacotherapy is an option for partial responders and nonresponders, but recent studies have cast doubts on the additional effect of medication [12,13]. Furthermore, use of medication entails several disadvantages, such as possible adverse effects, a heightened chance of relapse by discontinuation, and unknown effects in the long term [14]. This highlights the need for new ways to improve treatment for pediatric OCD.

Second, there are organizational and practical barriers to treatment. Particularly in remote areas, CBT is not always available, and in many places, there has been a long tradition of a shortage of experienced therapists and long waitlists for treatment [15-18]. Practical problems with scheduling, treatment associated costs, disorder-specific symptoms that restrict mobility, shame, and stigma can further limit accessibility to treatment [16,19-22].

In parallel, the use of digital technology in child mental health care is rapidly increasing [23]. Technologies (computers, internet, mobile devices, and apps) offer a unique opportunity to address several limitations associated with traditional treatment, such as access, suitability, expense, and stigma. In addition, new technologies can be appealing to children and adolescents, which may increase treatment compliance and motivation.

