### Study Procedures

All participants receive eCBT. For participants not having a smartphone and for those using an iPhone, an Android smartphone will be lent for the purpose of the study. Concurrent medication is allowed and will be reported during the study. Ongoing psychological treatment for OCD other than eCBT is not allowed. Participants can leave the study at any time for any reason if they wish to do so without any consequences. The investigator can decide to withdraw a participant from the study for urgent medical reasons. The following stop rules for study participation are applied: (1) problems other than OCD requiring acute other treatment (eg, severe depression and suicidal ideation) and (2) severe increase in OCD symptoms and insufficient response to eCBT treatment. Figure 3 shows the flow diagram of the study.

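### The noninferiority test compares raw CY-BOCS change with a nonrandomised historical cohort and does not adjust for baseline severity, which the trial measures

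*Protocol article*

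**What the plan says.** Study Design and Sample Size describes the design: "This study is an open trial using a historical control design to explore the feasibility, acceptability, and effectiveness of eCBT". For noninferiority, the CY-BOCS outcome "will be compared to data collected in the NordLOTS".

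The Statistical Analysis section fixes the method as an unpaired t test of raw change scores, in these words: "test will be performed to compare the treatment outcome (difference in the CY-BOCS score before and after treatment) in this study". NordLOTS is the comparator, the comparison being made "with the treatment outcome reported for the NordLOTS". It names no covariate, matching or weighting for this step. The linear mixed models in the same section have time as their only stated independent factor and are not described as including NordLOTS patients.

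The later Sample Size section gives a "noninferiority margin set at 4 points on the CY-BOCS" and 21 participants per arm for 80% power. It states neither the SD nor the significance level.

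Three other places bear on the choice:
- Background says of standardised CBT that "average symptom improvement is about 50%, with large individual differences".
- Table 1 schedules the CY-BOCS before and after treatment, rated by an independent evaluator.
- Study Procedures says: "Concurrent medication is allowed and will be reported during the study".

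**The concern.** Nothing in a historical comparison balances baseline severity between the cohorts. The article describes CBT benefit as a percentage of the starting score. If that is roughly how it works, patients who start higher lose more points under the same treatment, and equal raw change means equal efficacy only when the two baseline means happen to agree.

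The direction depends on the cohorts. A more severe eCBT sample would flatter eCBT and could hide a real deficit. A milder one would make eCBT look worse and could prevent a correct finding of noninferiority. The covariate that addresses this is already collected from every participant and is part of the entry criteria, but the named test does not use it. As this is an analysis the article specifies, it is not a detail left to an unseen document.

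**Working it through.** **1. The plan's own figure.** With true difference 0, n per arm = 2·SD²·(z_α + z_β)² / margin². SD and alpha are not stated, so I solved for the SD at 80% power and a margin of 4:
- one-sided 0.05, SD 5.2: 2 × 27.04 × 6.18 / 16 = 20.9, giving 21;
- one-sided 0.025, SD 4.6: 2 × 21.16 × 7.85 / 16 = 20.8, giving 21.

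So 21 is reachable with an SD of about 5.1-5.2 or 4.5-4.6 respectively. It can be neither confirmed nor called wrong. These SDs are used below.

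**2. Bias in mean change.** Bias = slope × difference in mean baseline. Reading the 50% average as a slope of 0.5 is an assumption.

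| Baseline difference | Bias (points) | Share of 4-point margin |
|---|---|---|
| 1 | 0.5 | 13% |
| 2 | 1.0 | 25% |
| 3 | 1.5 | 38% |
| 4 | 2.0 | 50% |
| 8 | 4.0 | 100% |

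**3. Range for the slope.** The slope of change on baseline is 1 − r × (post SD / pre SD). Assumed ranges: r 0.3-0.5, pre SD 4-5, post SD 5-8.
- Lowest: 1 − 0.5 × 8/4 = 0.
- Highest: 1 − 0.3 × 5/5 = 0.7.

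A 4-point baseline difference therefore gives a bias of 0 to 2.8 points. A bias equal to the margin needs a difference of 8 points at slope 0.5 and 4/0.7 = 5.7 points at slope 0.7.

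**4. Error rates at 21 per arm.** Let b be the bias in favour of eCBT and SE = SD × √(2/21). False noninferiority at a true 4-point deficit is Φ(b/SE − z_α). Power at a true difference of 0 is Φ((4 + b)/SE − z_α). For SD 5.2, SE = 1.605 and z_α = 1.645:
- false noninferiority, b = +1: Φ(0.623 − 1.645) = 15.3%;
- false noninferiority, b = +2: Φ(1.246 − 1.645) = 34.5%;
- power, b = −1: Φ(1.869 − 1.645) = 58.9%;
- power, b = −2: Φ(1.246 − 1.645) = 34.5%.

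| Setting | False noninferiority at b = 0, +1, +2 | Power at b = 0, −1, −2 |
|---|---|---|
| SD 5.2, one-sided 0.05 | 5.0%, 15.3%, 34.5% | 80.2%, 58.9%, 34.5% |
| SD 4.6, one-sided 0.025 | 2.5%, 10.5%, 29.1% | 80.4%, 56.1%, 29.1% |

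A larger sample does not help against false noninferiority. With 30 per group, SD 4.6 and one-sided 0.025, the rates are 2.5%, 13.2% and 39.1%, because the SE shrinks while the bias stays. With an assumed SD of 8.0 at 21 per arm and one-sided 0.05, they are 5.0%, 10.8% and 20.2%.

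**5. Precision.** Adjustment multiplies the SD by √[post²(1 − r²) / (pre² + post² − 2·r·pre·post)]. Over the ranges in step 3 this runs from 0.81 (r 0.3, SDs 5 and 5) to 1.00 (r 0.5, SDs 4 and 8), a reduction of 0-19%. This is a secondary gain.

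**The case against.** The strongest reply is that no imbalance has been shown. The article gives no NordLOTS baseline mean, age distribution, medication status or entry rule, so whether bias exists depends on a source outside the document. That stands, and the point is therefore conditional.

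The slope of 0.5 is also open to challenge. A 50% average improvement is a mean, reported with large individual variation, not a regression of change on baseline. At one corner of the assumed ranges the slope is 0, and adjustment then neither removes bias nor improves precision. This too stands, which is why a range is given.

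A third reply is that the study is mainly about acceptability and feasibility, calls the noninferiority work exploratory and foresees a later randomised trial. This lowers the stakes. But noninferiority is one of four stated hypotheses, the CY-BOCS is a primary outcome, and the comparison has its own margin and power statement.

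Finally, adjustment cannot deal with era, site or other unmeasured differences, and ANCOVA assumes that patients with the same baseline score are comparable across cohorts. Both are true. They call for a caveat and a retained unadjusted analysis, not for ignoring a measured confounder.

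**Conclusion.** The point holds as a weakness in a stated analysis. If mean baselines differ by 2 to 4 points, raw change is biased by about 1 to 2 points at slope 0.5. Under the first setting in the table, that is enough to multiply the false noninferiority rate by about three to seven, or to cut power to between 59% and 35%. The result rests on the assumed slope, the back-solved SD and an assumed baseline difference.

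A reader might infer more, and the document does not support it:
- **A bias as large as the margin.** At slope 0.5 that needs an 8-point gap in mean baseline, and nothing suggests one.
- **Confounding by medication.** Concurrent medication is allowed in eCBT, but its use in NordLOTS and its effect size are not given, and Background itself doubts that it adds benefit to CBT.
- **A contradiction about the comparator.** Data collected in NordLOTS (Study Design and Sample Size) and the outcome reported for it (Statistical Analysis) are compatible descriptions. They only leave open whether patient-level data will be used.

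**What to change.** State which NordLOTS data will be used, then:

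1. **Patient-level data available:** make the noninferiority comparison an ANCOVA of post-treatment CY-BOCS on study, with baseline CY-BOCS as covariate, and set the adjusted confidence interval against the 4-point margin.
2. **Only published summaries available:** regress eCBT change on baseline CY-BOCS, predict mean change at the NordLOTS baseline mean, and compare it with the published NordLOTS change. Carry the uncertainty of both estimates into the interval.
3. **Sensitivity analyses:** keep the unadjusted t test. Where patient-level data allow, add age and medication use.
4. **Reporting:** show both cohorts' baseline CY-BOCS side by side and say that unmeasured differences remain.

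The cost is a change of wording and slightly more analysis, with nothing further to collect from eCBT participants. The first option depends on access to patient-level NordLOTS data, which the article does not establish. The second needs the published baseline mean, and the change with its standard error.
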